## Methods/design

The study is currently underway at the Neonatal Intensive Care Unit (NICU) of the University of Turin, and has been approved by Local Ethic Committee. Informed written consent is obtained from parents before enrollment. The trial was registered on ISRCTN Registry BioMed Central (Registration number: ISRCTN70022881).

### Study population

All patients admitted to our unit that met the following inclusion criteria were consecutively enrolled in the study.

Inclusion criteria:Gestational age < 32 weeks or birthweight <1500 gExclusive feeding with human milk (fresh own mother’s or donor milk)Human milk volume > 80 ml/kg/day within the first 4 weeks of life

Exclusion criteria:Severe gastrointestinal pathologies (diagnosed or suspected necrotizing enterocolitis, colostomy, intestinal obstruction, symptoms of peritonitis, presence of blood in the feces)Chromosomal abnormalities or major malformationsHereditary metabolic diseasesIntravascular disseminated coagulopathy (IDC), shockPatent Ductus Arteriosus (PDA) requiring medical care or surgery at time of randomizationSevere renal failure (serum creatinine >2 mg/dl)

### Study design

Infants meeting inclusion criteria are identified and their parents approached for consent. After informed written parental consent is obtained, infants are randomized 1:1 by a software-generated list in one of the following groups:Control group: Adjustable Fortification with commercial multi-component fortifier (FM85 Nestlè) and protein concentrate (Protifar Nutricia), named BMC and BPC respectively, derived from bovine milk, for a minimum of 21 days (if necessary, fortification is continued after this period using the same type of product)Fortilat group: Adjustable Fortification with multi-component fortifier and protein concentrate derived from donkey milk, named DMC and DPC respectively, not commercially available, and prepared according to current EU legislation on Foods for special medical purposes, for a minimum of 21 days (if necessary, fortification is continued after this period using the same type of product).

The composition of BMC and DMC are provided in Table 1. Table 2 presents the composition of BPC and DPC. The experimental products were produced by ultrafiltration of pasteurized donkey milk in a pilot stainless steel plant. Retentates from the ultrafiltration processes were then pasteurized and aseptically lyophilized and packed. All the batches used for the trial were analyzed for the microbiological and chemical profile and complied with the safety criteria required by Italian legislation. The products are stored at −80 °C until used.

**Table 1 Tab1:** Macro-composition of the multi-component fortifiers derived from bovine milk (BMC) and from donkey milk (DMC). Values per 100 g of product

	BMC	DMC
Protein g (Nx6.25)	20.0	22.5
Carbohydrate g	66.0	59.0
of which:		
Lactose g	6.0	59.0
Maltodextrine g	60.0	0.0
Fat g	0.4	3.6
Energy:		
Kcal	385	390
kcal/g protein	18.8	15.6
Calcium mg	1500	938
Phosphate mg	900	734
Osmolality mOsm/Kg	453	441

**Table 2 Tab2:** Composition of the protein concentrates derived from bovine milk (BPC) and from donkey milk (DPC). Values per 100 g of product

	BPC	DPC
Protein g (Nx6.25)	88.5	43
Carbohydrate g	<1.5	33.5
Fat g	≤2.0	6.1
Energy Kcal	370	418
Calcium mg	1350	1650
Phosphate mg	700	1150

A nutrition protocol following the criteria of ADJ fortification is being followed to ensure that fortification advancement is consistent for all study participants. Tables 3 and 4 show the ADJ Fortification criteria for the control products (BMC and BPC) and for the test products (DMC and DPC). Since the protein concentration and energy content of the bovine milk based products differ from the donkey milk based products, the amounts of powder required to obtain the same level of fortification are different depending on the product in use (Table 4). Because the same nurses in charge of feeds preparation and administration are also in charge of evaluating signs of feeding tolerance, it is not possible to achieve a double blindness of the intervention. As caregivers are aware of the group allocation of infants, this is to be defined as a single-blind randomized controlled trial.

**Table 3 Tab3:** Adjustable Fortification criteria based on weekly blood urea nitrogen (BUN) values

BUN (blood urea nitrogen)	
< 10 mg/dl	Increase fortification by one level
10–16 mg/dl	No change
> 16 mg/dl	Decrease fortification by one level

**Table 4 Tab4:** Amount of fortifer and protein supplement at the various fortification levels, according to ADJ fortification protocol

	Multicomponent			Protein concentrate	
Levels	BMC g/ml	DMC g/ml		BPC g/ml	DPC g/ml
2.5%	0.025	0.02		–	–
4%	0.04	0.032		–	–
5%	0.05	0.04		–	–
5% +1	0.05	0.04	+	0.004	0.008
5% +2	0.05	0.04	+	0.008	0.016
5% +3	0.05	0.04	+	0.012	0.024

Advancing of enteral feeds is strictly regulated according to the feeding protocol adopted in our NICU, based on the evaluation of signs of feeding intolerance (available on demand to the authors). The criteria for hospital discharge are uniform, i.e., satisfactory weight gain while receiving full oral feeding, maintenance of adequate thermal stability and resolution of acute medical conditions.

### Outcome measures

Primary Endpoint.Occurrence of at least one episode of feeding intolerance, defined as interruption of enteral feeding for at least eight consecutive hours during the observation period.Secondary Endpoints.2.1 Gastrointestinal outcomes: Number of feeding intolerance episodes, number of feeding interruption episodes (of any duration), total hours of enteral feeding interruption, time required to reach full enteral feeding (150 ml/kg/day).2.2 Gastric Emptying time (ultrasonic measurements of the antral cross sectional area) [25, 26]: half-time of gastric emptying (minutes) and time of gastric emptying (minutes).2.3 Esophageal impedance and pH monitoring (MII/pH) [27, 28]: GER frequency (reflux events/h), bolus reflux extent (number of channels), Bolus clearance time (seconds), bolus exposure index and reflux index (percentage).2.4 Clinical outcomes: necrotizing enterocolitis, suspected or confirmed sepsis, mortality, hospital stay duration, intraventricular hemorrhage, retinopathy of prematurity (defined according to the Vermont Oxford Network) [29].2.5 Metabolic and auxological outcomes (as shown in the synoptic table) (Table 5).

**Table 5 Tab5:** Synoptic table. T0: before starting the fortification; T1: day 7 after beginning the fortification (if level 3 of ADJ fortification) or as soon as level 3 is reached; T2: day 14 since beginning of fortification; T3: day 21 since beginning of fortification

	STUDY PERIOD						
	Enrolment	Allocation	Post-allocation				Close-out
Timepoint			T0	T1	T2	T3	
Enrolment:							
Eligibility screen	X						
Informed consent	X						
Full patient history collection	X						
Allocation		X					
Intervention:							
BUN			X	X	X	X	
Albumin			X	X	X	X	
Creatinine			X	X	X	X	
Calcium			X	X	X	X	
Phosphate			X	X	X	X	
Alkaline Phosphatase			X	X	X	X	
Weight			X	X	X	X	
Lenght			X	X	X	X	
Head circumference			X	X	X	X	
Plasma Aminoacids			X			X	
Urine Aminoacids			X			X	
Urinary Metabolomic Profile			X			X	
Calprotectin			X			X	
pH			X	X	X	X	
BE			X	X	X	X	
HCO_3_^−^			X	X	X	X	
MII/pH						X	
Gastric emptying time						X	
Assesments							
List other data variables							X
List other data variables							X

### Sample size

The sample size has been determined based on the occurrence of primary endpoint (at least one episode of interruption of enteral feeding ≥8 h). Based on the data available in our NICU from the population of VLBWI or preterm infants, about 45% of infants present at least one interruption of enteral feeding ≥8 h.

In the hypothesis that the use of a better tolerated fortifier causes a 25% reduction in the frequency of the primary endpoint, and setting the risk of type I errors and the power at the usual 5 and 80%, 62 newborns per group have been considered as required.

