### Estimated rate of loss to follow up

Our NICU is a tertiary level neonatal unit. Most babies in the NICU stay until discharge from hospital. Very few infants return to local hospitals prior to discharge home, and it generally is very rare that they are transferred prior to 35 weeks corrected gestational age. In addition, all infants that meet inclusion criteria for the study are planned to be followed until two years of age, as part of our follow-up program. We therefore do not expect any significant loss to follow up.

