### Statistical analysis

The statistical analysis will be performed by the Medical Statistics and Biometry Unit of the Clinical and Community Sciences of the University of Milan.

At the end of the recruitment, the occurrence of the primary endpoint will be evaluated on the intention-to-treat population (all randomized infants). The comparison between the two study groups will be performed with the exact Fisher test. All secondary endpoints will be modelled in the framework of generalised linear model [30] allowing, when appropriate, for relevant covariates. The number of episodes of feeding intolerance (0, 1 … k) will be modelled as a Poisson variable. Total hours of enteral feeding interruption, time required to reach full enteral feeding, hospital stay duration, gastric emptying time and MII/pH parameters will be modelled (after proper scale transformation, if required) as normal variables. The occurrence of clinical outcomes, assesed as dychotomous variable (yes/no) will be modelled as binomial variables. Metabolic and auxological outcomes, which are repeatedly during study period, will be modelled (after proper scale transformation, if required) as normal variables, with a model allowing for repeated measures. All statistical models are fit with SAS software [31].

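### The sample size of 62 per group fits a fall of 25 percentage points (45% to 20%), but the protocol words it as a 25% reduction, for which power is about 20%, not 80%

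*Protocol article*

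**What the plan says.** The Sample size section of the protocol article bases the calculation on the primary endpoint, at least one interruption of enteral feeding of 8 hours or more. From the unit's own data, "about 45% of infants present at least one interruption of enteral feeding ≥8 h". The assumed effect is that "a better tolerated fortifier causes a 25% reduction in the frequency of the primary endpoint". The error rates are given by "setting the risk of type I errors and the power at the usual 5 and 80" percent, and the result is that "62 newborns per group have been considered as required".

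The section gives no target rate for the donkey-milk group. It does not say whether the 25% is relative or in percentage points, whether the test is one- or two-sided, or which formula was used. Three other places bear on the calculation:

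- Study design: "infants are randomized 1:1 by a software-generated list".
- Statistical analysis: "The comparison between the two study groups will be performed with the exact Fisher test".
- Estimated rate of loss to follow up: "We therefore do not expect any significant loss to follow up". So no inflation for dropout enters the figure.

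**The concern.** A percentage reduction applied to a frequency is normally read as proportional. Three quarters of 45% is 33.75%, an absolute difference of 11.25 points. A sample of 62 per group is far too small to give 80% power for a difference of that size between two proportions in this range. Either the effect is misworded or the power is wrong.

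This is the trial's only sample-size justification. If the effect as worded is the true one, the trial would miss it about four times in five. A report that repeated 80% power for a 25% reduction beside a non-significant result could lead readers to think an effect of that size had been ruled out, when the trial could hardly have detected it.

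**Working it through.** **Inputs.** Control rate p1 = 0.45, type I error 0.05, power 0.80 and 62 per group come from the Sample size section. The 1:1 allocation comes from Study design, and the Fisher exact test from Statistical analysis. A two-sided test is assumed because the protocol does not state the sidedness. The standard normal quantiles are 1.960 and 0.842.

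**Formulas.** With d = p1 − p2 and p̄ = (p1 + p2)/2:

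- Uncorrected: n = [1.960·√(2p̄(1−p̄)) + 0.842·√(p1(1−p1) + p2(1−p2))]² / d²
- Continuity-corrected: n_c = (n/4)·[1 + √(1 + 4/(n·d))]²

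**Step 1: reproduce 62.** Take the 25% as percentage points, so p2 = 0.20, d = 0.25 and p̄ = 0.325.

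- 1.960·√0.43875 = 1.298 and 0.842·√0.4075 = 0.537
- n = (1.298 + 0.537)² / 0.0625 = 53.9, so 54
- n_c = (53.9/4)·[1 + √(1 + 0.297)]² = 61.6, so **62**

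The continuity-corrected value is the protocol's figure. The relative size of this effect is 0.25/0.45 = 56%.

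**Step 2: the effect as worded.** p2 = 0.45 × 0.75 = 0.3375, d = 0.1125 and p̄ = 0.39375.

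- 1.960·√0.47742 = 1.354 and 0.842·√0.47109 = 0.578
- n = (1.354 + 0.578)² / 0.012656 = 294.9, so **295**
- n_c = (294.9/4)·[1 + √(1 + 0.1206)]² = 312.4, so **313**

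**Step 3: power at 62 per group.** The Fisher power sums the binomial probabilities of all outcome tables with two-sided p ≤ 0.05.

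| Effect | Fisher exact | Normal, continuity-corrected | Normal, uncorrected |
|---|---|---|---|
| 45% vs 20% | 80.9% | 80.3% | 85.3% |
| 45% vs 33.75% | 20.3% | 19.3% | 24.7% |

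**Step 4: can another convention rescue the relative reading?** One-sided testing gives 233 uncorrected and 250 corrected. Unpooled-variance and arcsine versions, one- or two-sided, also come nowhere near 62. The smallest value found is 231 (unpooled, one-sided). One-sided Fisher power at 62 is still only 29.9%. On the absolute reading, one-sided testing gives 43 or 51, so 62 also points to a two-sided calculation.

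**Step 5: what the trial can detect.** Suppose 28/62 control infants (45%) have the event.

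- 21/62 in the donkey-milk group (34%) is an observed relative reduction of exactly 25%, with Fisher p = 0.27.
- 17/62 gives p = 0.061.
- 16/62 (26%, an observed relative reduction of 43%) gives p = 0.038 and is the first significant result.

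Even a true fall from 45% to 25%, a 44% relative reduction, has only 58% power.

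**The case against.** The best defence is that the authors meant percentage points. The assumed effect follows directly on a rate expressed as a percentage of infants. On that reading every number agrees, and the size suits the planned Fisher test. The exact match supports this: the calculation was probably done correctly and only its description is loose. It can be added that no formula is shown, so the origin of 62 is inferred. The protocol nowhere proposes to treat a null result as excluding an effect. The article condenses a fuller protocol that may state the scale. The remedy leaves the design untouched.

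Much of this stands. The arithmetic is sound for a 25-point fall, the route to 62 is an inference from an exact match, and misreading a null result is a risk, not something the protocol plans. What does not stand is that the sentence can remain. The article states an effect rather than leaving it to another document, and its ordinary meaning is a relative reduction. No version of that reading comes near 62. The two readings differ about five-fold in sample size (313/62 ≈ 5) and about four-fold in power (80.9/20.3 ≈ 4), and a reader can tell them apart only by reworking the calculation.

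**Conclusion.** The concern holds. As worded, the protocol attaches 80% power to an effect for which the trial has about 20%: 20.3% with the planned Fisher test, and 19.3% to 24.7% with normal approximations. The 62 per group fits a fall from 45% to 20%, a 56% relative reduction. The conclusion assumes the 45% control rate, a two-sided 5% test and no dropout. One-sided testing does not rescue it (29.9%). The error lies in how the effect is described, not in the arithmetic for a 25-point fall. It still needs correcting, because the primary hypothesis and any later reading of a null result depend on this sentence.

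**What to change.** Reword the assumption in the Sample size section, for example:

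*We assume an absolute reduction of 25 percentage points in the primary endpoint, from 45% to 20% (a relative reduction of 56%). With a two-sided 5% type I error and 80% power, 62 infants per group are required (continuity-corrected formula). For a relative reduction of 25% (45% to 33.75%), power at this sample size is about 20%, so a non-significant result would not exclude an effect of that size.*

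The authors should confirm from their own records that 45% to 20%, two-sided, was the calculation made. If a relative reduction of 25% was really intended, the 80% claim has to be withdrawn, because that effect would need about 295 to 313 per group.

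The cost is a few sentences. The total stays at 2 × 62 = 124, and the endpoint, test and analysis population do not change. The only price is that the stated detectable effect looks less favourable.

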### Planned recruitment rate and compliance

In the year 2014, 115 infants less than 32 weeks gestation and weighting less than 1500 g were admitted to our NICU. Breastfeeding initiation rates with mothers’ own milk or donor milk were around 90% in our nursery. Therefore, around 100 infants per year were estimated to be eligible for the study, with a recruitment rate higher than 60%. We did not anticipate problems with compliance. The majority of mothers visits their baby on a regular basis, hence they are easily approached for consent as soon as the infant reaches the point to start fortification. Blood sampling required by the study protocol is consistent with the routine monitoring performed in our unit, hence there is no supplementary inconvenience for the patients and it is easily accepted by parents.

### Data collection methods

In order to promote the data quality, it has been provided a training plan for the nurses and clinicians based on fortification protocols and evaluation of feeding tolerance. Data are being collected according to the scheme shown in the synoptic table of the study (Table 5). Weight, length and head circumference measurements are recorded at birth, and during the observation period (weight: daily; length and head circumference: weekly), at 36 ± 1 weeks of postmenstrual age, 40 ± 1 weeks of postmenstrual age, at 6, 12 and 18 months of corrected age. The collection of outcomes, baseline, and other trial data are reported in the specific form by copying them from the medical record at discharge of the newborn.

### Estimated rate of loss to follow up

Our NICU is a tertiary level neonatal unit. Most babies in the NICU stay until discharge from hospital. Very few infants return to local hospitals prior to discharge home, and it generally is very rare that they are transferred prior to 35 weeks corrected gestational age. In addition, all infants that meet inclusion criteria for the study are planned to be followed until two years of age, as part of our follow-up program. We therefore do not expect any significant loss to follow up.

### Statistical analysis

The statistical analysis will be performed by the Medical Statistics and Biometry Unit of the Clinical and Community Sciences of the University of Milan.

At the end of the recruitment, the occurrence of the primary endpoint will be evaluated on the intention-to-treat population (all randomized infants). The comparison between the two study groups will be performed with the exact Fisher test. All secondary endpoints will be modelled in the framework of generalised linear model [30] allowing, when appropriate, for relevant covariates. The number of episodes of feeding intolerance (0, 1 … k) will be modelled as a Poisson variable. Total hours of enteral feeding interruption, time required to reach full enteral feeding, hospital stay duration, gastric emptying time and MII/pH parameters will be modelled (after proper scale transformation, if required) as normal variables. The occurrence of clinical outcomes, assesed as dychotomous variable (yes/no) will be modelled as binomial variables. Metabolic and auxological outcomes, which are repeatedly during study period, will be modelled (after proper scale transformation, if required) as normal variables, with a model allowing for repeated measures. All statistical models are fit with SAS software [31].

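### The primary endpoint gets only an unadjusted Fisher exact test: valid and adequately powered on the plan's own figures, but it gives up power that a pre-specified adjusted analysis would recover

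*Protocol article*

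**What the plan says.** The Statistical analysis section of the protocol article takes the primary endpoint (at least one feeding interruption of eight hours or more) first. The analysis set is stated: "the occurrence of the primary endpoint will be evaluated on the intention-to-treat population (all randomized infants"). The test follows: "The comparison between the two study groups will be performed with the exact Fisher test". No covariate, stratum or effect estimate is attached to it.

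The next sentence treats the other endpoints differently: "All secondary endpoints will be modelled in the framework of generalised linear model [30] allowing, when appropriate, for relevant covariates". Dichotomous clinical outcomes are to be modelled as binomial, so a regression for a binary outcome is already part of the plan, but not for the primary one.

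Under Sample size, the control rate is given as "about 45% of infants present at least one interruption of enteral feeding ≥8 h", the hypothesis is that the new fortifier "causes a 25% reduction in the frequency of the primary endpoint", and the result is "setting the risk of type I errors and the power at the usual 5 and 80%, 62 newborns per group have been considered as required". Under Study design, "infants are randomized 1:1 by a software-generated list"; the article does not say whether the list was stratified.

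**The concern.** The plan budgets a 5% type I error for its one confirmatory comparison and then names a test that spends clearly less at this sample size. It also reserves covariates for endpoints that carry less weight. Gestational age and birthweight define eligibility and should be available for every infant, and the Data collection methods section has weight recorded at birth. Using them would need no new measurement. If either predicts feeding interruption, an adjusted comparison has more power with the same 124 infants.

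What is at stake is a borderline result. With 28/62 against 17/62 events, for instance, the two-sided Fisher p-value is 0.061 and the mid-p value is 0.043. The choice of test alone can then decide the conclusion.

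**Working it through.** **Inputs.** From Sample size: control rate 0.45, a 25% reduction, type I error 5%, power 80%, 62 per group. From Statistical analysis: Fisher's exact test on all randomised infants, so 62 against 62. Sidedness is not stated; two-sided is assumed. The strength of association between maturity and the endpoint is not given; it is assumed as an odds ratio (OR) of 1, 1.5, 2 or 3 per SD of one baseline covariate.

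**Step 1: reproduce 62.** Read the reduction as 25 percentage points (0.45 vs 0.20, mean 0.325).
- Uncorrected: n = [1.960·√(2·0.325·0.675) + 0.842·√(0.45·0.55 + 0.20·0.80)]² / 0.25² = 53.9, rounded up to 54.
- Continuity-corrected: n′ = (n/4)·[1 + √(1 + 4/(n·0.25))]² = (53.9/4)·[1 + √(1 + 4/13.48)]² = 61.6, rounded up to 62.

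The stated figure is matched exactly. The continuity-corrected formula approximates Fisher's test, so sample size and named test agree. A relative reduction (0.45 vs 0.3375) would need 295 per group, or 313 with the correction, so it is not the reading behind 62.

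**Step 2: true size at 62 vs 62.** Size(p) is the sum of Bin(x; 62, p)·Bin(y; 62, p) over all tables (x, y) with test p-value at most 0.05.

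| Common rate | Fisher | Mid-p |
|---|---|---|
| 0.20 | 2.9% | 4.7% |
| 0.325 | 3.2% | 4.7% |
| 0.45 | 3.7% | 4.8% |
| 0.50 | 3.8% | 4.4% |

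Fisher's size never exceeds 3.84% at any common rate. Mid-p peaks at about 5.1% (near 0.40) among the rates checked. A Boschloo-type exact test has a maximum size of 4.99%.

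**Step 3: power at 0.45 vs 0.20.** The same sum with different rates gives Fisher 80.9%, mid-p 84.9% and Boschloo-type 84.9%. The cost of Fisher's conservatism is 84.9 − 80.9 = 4.0 points, and this figure involves no simulation. If the true effect is smaller (0.45 vs 0.25), Fisher has 58.3% and mid-p 64.8%, a gap of 6.5 points.

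**Step 4: what adjustment adds.** Logistic regression on arm and one standardised covariate, 5,000 simulated trials per scenario, 62 per arm, marginal rates 0.45 vs 0.20, Wald test:

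| OR per SD (assumed) | Power, Wald | Gain over OR 1 | Size at 0.45 | Size at 0.20 |
|---|---|---|---|---|
| 1 | 85.2% | – | 5.0% | 4.4% |
| 1.5 | 86.8% | 1.7 | 4.9% | 4.4% |
| 2 | 87.7% | 2.6 | 5.2% | 4.6% |
| 3 | 91.2% | 6.0 | 4.6% | 5.1% |

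The Monte Carlo standard error is about √(0.88·0.12/5000) = 0.5 points for power and √(0.05·0.95/5000) = 0.3 points for size. Subtracting Fisher's power in the same simulated trials removes shared noise: the Wald-minus-Fisher differences are 4.5, 6.0, 7.7 and 9.4 points, so the gains over OR 1 become 1.5, 3.1 and 4.9. Adjustment as such is therefore worth roughly 1 to 6 points over this range. The likelihood-ratio version ran at 4.9% to 5.8%, slightly less well controlled.

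**Step 5: is the model small enough?** Expected events under the plan are 62·0.45 + 62·0.20 = 40.3. With three slopes (arm, gestational age, birthweight) that is about 13 events per coefficient, workable with linear terms.

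**The case against.** The strongest reply is that nothing here is wrong. Fisher's test keeps its size below 5%, the sample size was evidently derived to suit it, and it delivers the 80% asked for. Preferring a more powerful test is a design preference, and an analysis plan that is not shown may add adjusted analyses. Much of this stands: the choice is defensible and the planned power is met. But the primary test is a stated choice, not a gap, and the same section shows that covariate models were available and assigned only to the secondary endpoints. An adjusted supportive analysis elsewhere would not change which test decides.

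A reader might also infer more than the article supports:
- *That the trial is underpowered or the test invalid.* Steps 1 to 3 show the opposite on the reading that reproduces 62.
- *That adjustment lifts power from about 80% to 87–92%.* About 4 points of that come from leaving Fisher, with no covariate at all; the rest depends on an assumed prognostic strength.
- *That Fisher is the weakest test on offer.* The Yates-corrected chi-square has the same power here, 80.9%.
- *That chance imbalance in maturity biases the result.* Under randomisation the error rate already allows for it. Adjustment improves precision; it does not remove a bias.
- *That siblings break the test.* The article says "All patients admitted to our unit that met the following inclusion criteria were consecutively enrolled" but mentions no multiple births, and it describes infants as being randomised individually. Under individual allocation Fisher's test keeps its size under no effect even if siblings' outcomes are correlated.

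The cost of changing is real too: the trial is under way, caregivers know the allocation, and a model-based test loses the exact guarantee.

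**Conclusion.** The point holds as a loss of efficiency. The primary test spends 2.9% to 3.8% of a 5% budget over common rates of 0.20 to 0.50, which costs 4 points of power at the planned effect (80.9% against about 85%). Leaving out baseline maturity costs roughly 1 to 6 points more.

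The first figure rests on two-sided testing, 62 per arm, and 45% against 20%. The second also assumes an odds ratio of 1.5 to 3 per SD for a single covariate; the article offers nothing to narrow that range, and the gain from using both covariates was not simulated separately. If a relative 25% reduction was meant, Fisher's power is about 20% and mid-p's about 25%. That would be a separate sample-size problem, which the choice of test does not solve.

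**What to change.** Before any unblinded analysis, and decided by people who have not seen outcomes by arm, amend the Statistical analysis section as follows:

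1. **Primary test:** logistic regression of the endpoint on arm, with gestational age and birthweight as pre-specified linear covariates, in all randomised infants. Name one p-value as decisive: the Wald test, or a permutation test that re-draws allocation under the scheme actually used.
2. **Effect measure:** the standardised risk difference with 95% CI, i.e. the mean over all infants of the predicted risk under the donkey-milk arm minus that under control. State the CI method, and state that the named p-value decides if the two disagree.
3. **Sensitivity:** the unadjusted comparison by Fisher (or mid-p).

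No extra infants or measurements are needed, and binomial models are already planned for other outcomes. The price is that, with the Wald test, the exact size guarantee becomes an approximate one (simulated size about 4.5% to 5.5%), and the change to the primary analysis of an ongoing trial must be dated, justified and reported. A permutation p-value that respects the allocation scheme would keep the guarantee. If the sponsor prefers to stay unadjusted, a Boschloo test alone recovers the 4 points while keeping size at or below 5%.

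### Siblings are not excluded, yet every stated analysis treats infants as independent: under individual randomisation this costs precision rather than validity, and a mother-level term would recover it

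*Protocol article*

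**What the plan says.** Enrolment (Protocol article, Study population): "All patients admitted to our unit that met the following inclusion criteria were consecutively enrolled in the study". Neither the inclusion nor the exclusion list mentions multiple births, so each eligible sibling enters.

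Allocation (Study design): "infants are randomized 1:1 by a software-generated list". The unit is the infant. No rule for siblings is given.

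Primary analysis (Statistical analysis): the set is all randomised infants, and "The comparison between the two study groups will be performed with the exact Fisher test".

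Secondary analyses (same section): "All secondary endpoints will be modelled in the framework of generalised linear model", with covariates where relevant. Counts are Poisson, times and physiological measures normal, clinical events binomial. Metabolic and growth outcomes are analysed "with a model allowing for repeated measures".

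Sample size: the control rate is given as "about 45% of infants present at least one interruption of enteral feeding" of at least eight hours, and the design requires 62 infants per group.

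**The concern.** Twins and triplets share gestational age, the time and unit of care and, when fed their own mother's milk, the milk that is being fortified. Growth, time to full feeds and length of stay are therefore likely to be correlated within a sibship. The repeated-measures model links visits of one infant; it does not link infants of one mother.

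Two things are at stake. First, a pair split between the arms gives a within-mother comparison that is more precise than a comparison of unrelated infants, and the stated models give it no extra weight. Second, whether the stated tests hold their nominal level depends on how siblings were allocated, and the article does not say.

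**Working it through.** **1. The plan's own figure.** For 45% against 20%, two-sided 5% and 80% power, the mean rate is 0.325. The uncorrected size per group is

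[1.96·√(2·0.325·0.675) + 0.8416·√(0.45·0.55 + 0.20·0.80)]² / 0.25² = (1.298 + 0.537)² / 0.0625 ≈ 53.9.

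The continuity correction gives (53.9/4)·[1 + √(1 + 4/(53.9·0.25))]² ≈ 61.6, that is 62. The stated figure is reproduced as a calculation for independent infants. Exact Fisher power at 62 per group is 80.9%. (This reads the 25% reduction as percentage points. The relative reading, 45% to 33.75%, needs 295 per group, or 313 with correction; that is a separate matter.)

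**2. Assumptions that the document does not supply.** Twins only; m = 12 to 22 pairs among N = 124 infants (24/124 = 19% to 44/124 = 35%); within-pair correlation r = 0.2 to 0.7; half the pairs split under individual randomisation.

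**3. Precision left unused under individual randomisation.** With N − 2m singletons, the information on the arm difference when pairs are modelled is

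(N − 2m)/4 + (m/2)·0.5/(1 − r) + (m/2)·0.5/(1 + r),

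against N/4 = 31 when they are not. The relative gain simplifies to (2m/N)·r²/(1 − r²).

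- 12 pairs, r = 0.5: 25 + 6 + 2 = 33; 33/31 = 1.065.
- 22 pairs, r = 0.7: 20 + 18.33 + 3.24 = 41.57; 41.57/31 = 1.341.

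| r | 12 pairs | 22 pairs |
|---|---|---|
| 0.2 | 0.8% | 1.5% |
| 0.3 | 1.9% | 3.5% |
| 0.5 | 6.5% | 11.8% |
| 0.7 | 18.6% | 34.1% |

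**4. Error in the stated standard errors under individual randomisation.** The true variance relative to the stated one is 1 + r·(2m/N)·(share of pairs in the same arm − share split). This averages about 1.00. Its chance SD is 2r√m/N: 2·0.2·√12/124 = 1.1% at the low end and 2·0.7·√22/124 = 5.3% at the high end, in either direction. On the standard-error scale that is about half as much, 0.6 to 2.6%.

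**5. If all pairs shared an arm.** The design effect is 1 + r·2m/N, and the true level of a nominal 5% test is 2·[1 − Φ(1.96/√DE)].

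- 12 pairs, r = 0.2: DE = 1.039, level 5.4%.
- 22 pairs, r = 0.7: DE = 1.248, level 7.9%.

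**6. The Fisher test by simulation** (124 infants; 20,000 runs at 45% in both arms, 10,000 at 45% against 20%). The latent correlations of 0.5 and 0.8 correspond to about 0.33 and 0.59 on the yes/no scale. The first three result columns give the type I error.

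| Infants in twin pairs | Individual | Kept together | All split | Power, individual |
|---|---|---|---|---|
| none | 0.040 | – | – | 0.81 |
| 30%, latent 0.5 | 0.039 | 0.053 | 0.029 | 0.81 |
| 40%, latent 0.8 | 0.037 | 0.072 | 0.017 | 0.80 |

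**The case against.** A reader might infer that twins make the trial's confidence intervals and p-values wrong, or that 62 per group is too few. The documents do not support either. The article describes infants being randomised from a list. Under individual allocation, same-arm and split pairs offset each other on average, the Fisher test keeps its level and power, and the chance error in a standard error is at most a few per cent. The levels above 5% need siblings to be kept together, which no passage states.

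It can also be said that a modelling framework leaves room for a mother-level effect in a full analysis plan, and that a journal article may leave sibling allocation to the full protocol. That is fair, and the missing sibling rule is not treated here as a fault in itself. Still, the article goes beyond a bare framework: it fixes the primary test, assigns a distribution to each type of secondary endpoint, and names one dependence structure. As stated, none of these accommodates siblings.

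Two further objections stand. Adjusting for gestational age or baseline size, which the covariate clause permits, would lower the residual sibling correlation and hence the gain. And clustered binomial models for uncommon events such as death or necrotising enterocolitis may be unstable with 124 infants in mostly single-infant clusters.

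**Conclusion.** The point holds as one of efficiency and robustness. Under individual randomisation the primary test is valid, standard errors are right on average, and the sample size needs no change. What is lost is information: negligible to small at correlations of 0.2 to 0.3 (about 1 to 3.5%), modest at 0.5 (6 to 12%), and worth having at 0.7 (19 to 34%), a level most plausible for the growth measures.

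All of these sizes rest on an assumed 20 to 35% of infants being twins and on assumed correlations, before any covariate adjustment. Anti-conservative testing (nominal 5% at about 5.4 to 7.9%; Fisher 0.053 or 0.072 in the two simulated scenarios) is conditional on siblings sharing an arm, which the article neither states nor excludes. A mother-level term gives sound standard errors under either allocation, so it is the better choice at almost no cost.

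**What to change.** Recruitment is described as under way and the analysis follows its end, so the analysis wording can still be settled.

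- Report how siblings were actually allocated. This can only be described, not set afterwards.
- Record a pregnancy identifier for each infant.
- Fit the growth, metabolic and other continuous or count secondary models with mother as the cluster: a random effect above the infant in the repeated-measures model, or a GEE with exchangeable working correlation and a small-sample correction.
- For rare yes/no outcomes, use clustering only where the model is stable.
- Keep the Fisher test as primary, and report a risk difference with mother-clustered standard error beside it as a sensitivity analysis.

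The cost is slightly more complex models and one identifier. No extra infants or procedures are needed. If siblings turn out to have been kept in one arm, the clustered analysis of the primary endpoint should carry the interpretation, because the Fisher p-value would then be too small.
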